#### Assessment

All assessments will be conducted by phone (EDE) or via a link provided by e-mail (EDE-Q, CIA, EQ-5D-5 L, WAI). The EDE will be conducted at start (week 0) and post treatment (week 12). These assessments will be conducted by research assistants who will be blinded. If blinding is broken, the assessment will still be completed, and the results compared with results of the other participants in the same condition. If the results of the participant with broken blinding are outliers, they will not be taken into account in the analyses. All other assessments will be conducted at start, during week 5, week 12 and at week 24 and 36 (see also Figs. 1 and 2). Since treatment effect is expected to continue after end of treatment [11, 12], follow up measures will be conducted. If a participant does not complete the online assessments they will be called by a research assistant in order to motivate them. All assessments will be processed in Castor EDC (https://www.castoredc.com/) which is ISO 27001/27002/9001 and NEN 7510 certified. In addition, staff conducting the assessments do not offer GSH-CBT-E themselves.

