### Outcome measures and assessment

#### Outcome measures

##### Primary outcome measure

The primary outcome measure will be difference in eating disorder pathology, operationalized as the amount of days binge eating occurred, post treatment versus the waiting list control condition. Due to the absence of purging behavior, participants experience difficulty to recall the number of binge eating episodes. Therefore, participants suffering from BED were asked to report the number of days binge eating occurred rather than number of episodes [26, 41]. This is in line with the primary outcome measure chosen in another study [41]. Amount of binge free days will be measured by the EDE [28] and EDE-Q [29]. If a discrepancy arises between binge free days on the EDE and EDE-Q, the EDE will be chosen over the EDE-Q, because it is the golden standard for assessing eating disorder pathology [42].

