### Statistical analysis

The number of binge free days, other eating disorder pathology, quality of life, clinical impairment and therapeutic alliance will be reported as means (standard deviations); and effect sizes between the two conditions will be reported as Cohen’s *d*. Direct costs of the eating disorder treatment will be reported in euros. Cost-effectiveness analysis with number of binge- free days as effect measure and a cost- utility analysis using QALYs will be performed. The QALYs will be derived from the Dutch version of EQ-5D-5 L [43]. Generalized Linear Mixed Models (GLMM) will be used for the analysis of intervention outcomes. The variable BMI 19.5 ≥ BMI < 30 and 30 ≥ BMI < 40 will be included in the GLMM models as covariate. Analyses will be conducted on the entire randomized sample (i.e. intention to treat), and on the per protocol/ treatment completers sample. The primary endpoint for the study is 12 weeks post-randomization. As there are no multiple primary endpoints, there will be no Bonferroni correction or other correction for the significance level applied. Missing data will be handled using multiple imputation. All analyses will be carried out using SPSS version 22+ and R version 3.0+ by an independent Arkin data processor. Results are planned to be published in international peer reviewed journals.

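### EDE results from unblinded assessments are discarded when they are outliers: an undefined, outcome-dependent exclusion on the primary outcome that does not fit intention to treat

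*Protocol article*

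**What the plan says.** The protocol article, under Assessment, has the EDE interview done by blinded research assistants at week 0 and week 12. It then gives a rule for failures of blinding: "If blinding is broken, the assessment will still be completed, and the results compared with results of the other participants in the same condition". The next sentence reads: "If the results of the participant with broken blinding are outliers, they will not be taken into account in the analyses". No numerical definition of an outlier follows, and the exclusion is not limited to a sensitivity analysis.

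Three other statements determine what this rule touches:

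- Under Primary outcome measure, binge days come from the EDE and the EDE-Q. Where the two disagree, "the EDE will be chosen over the EDE-Q, because it is the golden standard for assessing eating disorder pathology".
- Under Statistical analysis, "The primary endpoint for the study is 12 weeks post-randomization".
- Under the same heading, "Analyses will be conducted on the entire randomized sample (i.e. intention to treat), and on the per protocol/ treatment completers sample". Missing data are to be multiply imputed. The outlier rule is not mentioned there.

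**The concern.** Whether an observation stays in the analysis depends on the observation itself, after randomization and relative to its own arm. Nobody can say in advance which values would go, because the cut-off is left open. That leaves discretion over primary outcome data.

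The rule also misses its purpose. The worry about a broken blind is that the assessor's rating drifts toward what the assessor expects. A drifted but unremarkable rating stays in under this rule, while an accurate but extreme rating goes out.

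At stake are the week-12 difference in binge days and its test. Trimming the tail of an arm lowers its estimated variance. If the two tails are trimmed unequally, the difference itself moves.

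**Working it through.** **Step 1. Which assessment is affected.** Randomization takes place after baseline (Randomization section), so the week-0 EDE cannot be unblinded to arm. That leaves the week-12 EDE. Week 12 is the primary endpoint and the EDE overrides the EDE-Q, so the rule acts on the primary outcome value.

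**Step 2. The plan's own figure.** The point rests on no stated figure, but the planned size sets the scale. With d = 0.47, two-sided α = 0.05 and 80% power, n per arm = 2(1.960 + 0.842)² / 0.47² = 71.1, so 72. The t-test version gives 72.04, with power 79.98% at 72. This reproduces the plan's 72 per arm (144). Then 144 × 1.25 = 180. The check below uses 72 per arm.

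**Step 3. Assumptions.** The documents give no unblinding rate, outlier cut-off or outcome distribution. Assumed here:

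- Binge days out of 28 are beta-binomial. The mean is 8 in both arms (SD about 6.7) for no effect, and 5 against 8 for a true effect of −3 days.
- An outlier lies beyond 2 SD, 1.5 IQR or 3 SD of its own arm.
- A discarded value is left out.
- The test is an unequal-variance t statistic, with 20,000 replicates per scenario.

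**Step 4. What one exclusion does.** Removing a value x from an arm with n results and mean m moves that mean by −(x − m)/(n − 1). For x = 24, m = 8, n = 72 this is −16/71 = −0.23 days. With a 2 SD rule the limits are 8 ± 13.3, or −5.3 and 21.3. The lower limit is below zero, so under this distribution only high values can be excluded.

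**Step 5. Results.** Unblinding is shown as treated % / waiting list %. Ranges run over the three cut-offs. A negative shift favours GSH CBT-E.

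| Unblinded | Shift, no effect (days) | Type I error, all kept | Type I error, rule applied | Added shift, true effect −3 (days) |
|---|---|---|---|---|
| 5 / 5 | 0.00 | 4.8–4.9% | 5.0–5.2% | −0.01 to −0.02 |
| 20 / 5 | 0.00 to −0.10 | 4.7–5.0% | 4.9–5.8% | −0.04 to −0.14 |
| 30 / 5 | −0.01 to −0.18 | 5.0–5.1% | 5.4–6.5% | −0.06 to −0.23 |
| 30 / 30 | 0.00 | 5.0–5.2% | 5.3–7.2% | −0.05 to −0.14 |
| 100 / 0 (extreme) | −0.02 to −0.71 | 4.9–5.4% | 5.6–14.4% | −0.21 to −0.90 |

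As a cross-check of the 30/5 row at 2 SD, on average 0.95 treated and 0.16 waiting-list results are dropped. If each lies about 16 days above its arm mean, the shift is (0.95 − 0.16) × 16/71 = 0.18 days, in line with the simulated 0.175.

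**Step 6. A second outcome model.** This uses a negative binomial with k = 1 and mean 6, capped at 28, with 4,000 replicates and no true effect.

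- 5% or 10% unblinded in both arms: no shift; type I error 4.9–5.9% against 4.7–5.7% without the rule.
- 20% against 5%, lenient cut-offs (2 SD or 1.5 IQR): −0.13 to −0.15 days and 6.1–6.4%.
- 20% against 5%, 3 SD: about −0.06 days and 5.4–5.9%.
- 50% against 10%, lenient cut-offs: about −0.4 days and about 9%. With 3 SD, type I error is 6.5–6.8%.

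**Step 7. Scale.** A shift of 0.175 days is 0.175/6.66 = 0.026 SD, against a planned effect of 0.47 SD.

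**The case against.** Several stronger conclusions might be inferred, and the documents do not carry them.

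*That the result is biased in favour of GSH CBT-E, with treatment failures removed mainly from that arm.* This needs unblinding to be more common in the treated arm. That is plausible, since treated participants have weekly phone sessions. But waiting-list participants also know their allocation, receive monitoring calls, and are about to start treatment at week 12, when the EDE is done. They too can reveal their arm. With equal rates and no true effect there is no mean shift.

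*That participants are dropped, so the analysis is certainly not intention to treat.* The pronoun in the rule most naturally refers to the results. The value might be imputed, or the week-12 EDE-Q used, with the participant kept in the sample. The article does not say so. Imputation would not in general repair the problem either: values deleted because of their size are not missing at random, and imputations would be drawn from a distribution whose extreme values had been removed.

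*That the damage is large.* Assessors are blinded and do not deliver the treatment, so unblinding may be rare. At 5% in both arms, fewer than one result in five trials is lost per arm (0.16 at most under no effect). The simulations use a t-test, whereas the plan has a mixed model adjusted for BMI stratum.

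*That the rule compromises the blinding of assessors.* An independent data processor runs the analyses and could compare results within arm without telling assessors anything.

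What stands after all this is the stated rule itself: selection on the outcome, no threshold, no restriction to a sensitivity analysis, and no reconciliation with intention to treat. A separate analysis plan could supply a cut-off, but it would not change the fact that the exclusion depends on the outcome.

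**Conclusion.** The concern holds as a fault in a stated rule. The protocol discards week-12 primary outcome values after randomization because of their size, by an undefined criterion. This is inconsistent with analysing everyone randomized and does not protect against assessor bias.

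The size and direction of bias cannot be fixed from the documents. Under the assumptions above it is negligible when unblinding is rare, and small when the cut-off is strict unless unblinding is very uneven. With 30% against 5% unblinded it is 0.01 to 0.18 days toward GSH CBT-E with type I error of 5.4 to 6.5%; at 20% against 5% it is generally smaller. With 30% in both arms there is no shift under the null, but type I error is 5.3 to 7.2%. Larger effects need extreme asymmetry. The case for change rests on the principle and on how easily the rule can be avoided, not on a demonstrated large bias.

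**What to change.** Before outcome data are examined by arm:

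1. Delete the outlier rule from the Assessment section.
2. Keep every EDE result in the primary intention-to-treat analysis, whatever the blinding status.
3. Record each broken blind and report the number by arm.
4. Add one sensitivity analysis that sets all unblinded week-12 EDE results to missing in both arms, regardless of value, and either multiply imputes them or uses the EDE-Q value in their place. It should stay a sensitivity analysis, because unblinding is itself a post-randomization event.

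The cost is one changed sentence and one extra analysis. The planned sample size does not change. In the simulations with all results kept, type I error under no effect was 4.7 to 5.4%, which is nominal apart from simulation error.

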**Fig. 1 Fig1:**
[figure not shown]
Flow chart of planned intervention and assessment

Participants are referred for treatment by general practitioners, secondary care health professionals or general hospitals. All potential participants are over 18 years of age and are being treated voluntarily. All potential participants classified with BED or OSFED BED, assessed by a clinical psychologist or psychiatrist, are invited to participate in the study. If a potential participant meets all inclusion and none of the exclusion criteria, agrees to the terms and conditions of the study and has provided informed consent, a baseline assessment (T0) will be scheduled. After the baseline assessment is completed, participants will be randomized to either the experimental condition (GSH CBT-E) or the waiting list control condition. Randomization will be blinded and stratified for body mass index (BMI) above or below 30. BMI will be calculated as weight in kg/ height in m^2^. Participants assigned to the experimental condition will start their treatment directly after they read the mandatory literature. The control group will start treatment after a waiting list period of 12 weeks, the same duration as the intervention. After baseline (T0), assessments will take place four times during and after treatment: at week 5, which is the evaluation-point of treatment for GSH CBT-E (T1); at the end of treatment for GSH CBT-E/ start of treatment for waiting list control group (week 12, T2); at 12 weeks after treatment for GSH CBT-E/ End of treatment for the waiting list condition (week 24, T3); and at 24 weeks after treatment for GSH CBT-E/, 12 weeks after treatment for waiting list control group (week 36, T4). The initial screening, before consent to study participation will take place at Novarum, but the intervention and assessments will take place at any location where participants have internet connection and are able to focus on their sessions. Since a large proportion of the Dutch population (96.7%) had internet access in 2018 [33], the participants’ personal location can be anywhere in the Netherlands. Obtained close- out period will be 1.5 years.

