### Intervention and procedure

All participants will receive GSH CBT-E: the experimental group will receive treatment immediately after baseline assessment, and the control group after a 12 weeks waiting period. GSH CBT-E is an online guided self-help version of CBT-Enhanced [8], based on *Overcoming Binge Eating, The Proven Program to Learn Why You Binge and How You Can Stop* [23], whose second part, a self-help guide, has been transformed into an online intervention.

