##### Intervention

GSH-CBT-E is based on Cognitive Behavioral Therapy- Enhanced, focused version, offered in a guided self-help format consisting of CBT-Enhanced key interventions, inevitably however less complex and with a shorter duration as in CBT-Enhanced focused. Before participants are eligible to start treatment, they have to read Part one of *Overcoming Binge Eating, The Proven Program to Learn Why You Binge and How You Can Stop* [23], or the Dutch translation *Overwin je eetbuien, waarom je te veel eet en hoe je daar mee kunt stoppen* [34]*.* This contains psycho-education about eating disorders and will be referred to during treatment. Participants will be asked if they have read part one before start of treatment. If the patient has not, they will be asked to read it during the first week(s) of treatment. In addition, before starting treatment, baseline assessment will take place. The EDE will be conducted by phone and participants will be sent a link to the self-report questionnaires, which they can complete at home on a computer. After baseline assessment and reading part one of *Overcoming Binge Eating The Proven Program to Learn Why You Binge and How You Can Stop* [23], the patient will be ready to start GSH CBT-E. Just like regular CBT-Enhanced, GSH CBT-E comprises three main stages; the first stage focuses on establishing regular eating and alternatives for binge-eating, using real-time self-monitoring as central intervention, and events, moods and eating. After joint review of progress & designing rest of treatment in the second stage, the third stages focuses on dietary restraint or shape concern and finally ending well with a firm focus on minimizing the risk of relapse in the long term. GSH CBT-E is a 12 week program. Once a week there will be a therapy session. All sessions will be conducted by phone. Participants have to start reading information online, to monitor their eating behavior, and to schedule, once a week, weighing, and, twice a week, self-evaluation sessions. The program is interactive, participants have to upload assignments and the therapist can monitor them. In addition, patient and therapist do interact weekly. Therefore, it differs from merely reading an e-book. A few days after start of treatment, participants will have a 20 min phone session with their therapist. To ensure consistency between therapists, these phone sessions are pre-scripted. During the first 4 weeks, participants will have to monitor their eating behavior, including their thoughts and feelings and establish a regular eating pattern. They will also introduce alternative activities for binge eating and work on problem-solving skills. During week 5, they will fill out assessment questionnaires, sent to them by a link, and their progress will be assessed, by both themselves and their therapist. This session will enable them to decide whether to add a module on body evaluation or dietary restraint during week 6–11 in addition to monitoring, regular eating, alternatives for binge eating and problem solving (Table 1). From week six onwards the program modifies to the user, based on the maintaining factors of their binge eating disorder. Before the 12th session participants will have to fill out the questionnaires. Results will be discussed during session 12, when they will also discuss what to do to prevent set-backs. The post treatment EDE will be conducted by phone. GSH CBT-E treatment will not be altered or interfered with during the study. As GSH CBT-E is a 100% guided self-help treatment without face to face sessions. After conclusion of the treatment, participants can still access the treatment module. To ensure data protection GSH- CBT-E is only available through a HTTPS protocol and secured by a 256-bit encrypted SSL- certificate. The online environment (Karify) is ISO 27001 and NEN 7510 certified.

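### The common visit calendar lists no trial assessment at the waiting-list arm's own treatment week 5, and a between-condition Cohen's d for therapeutic alliance cannot be interpreted at any shared trial week

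*Protocol article*

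**What the plan says.** The Assessment section lists the forms delivered "via a link provided by e-mail (EDE-Q, CIA, EQ-5D-5 L, WAI"). Apart from the EDE interview, which is held at weeks 0 and 12, it gives one timetable: "All other assessments will be conducted at start, during week 5, week 12 and at week 24 and 36". It makes no distinction by arm or by form.

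The Trial design section explains what each visit means. The second and third post-randomization visits have a meaning in both arms: "at the end of treatment for GSH CBT-E/ start of treatment for waiting list control group (week 12, T2") and "at 12 weeks after treatment for GSH CBT-E/ End of treatment for the waiting list condition (week 24, T3"). The week-36 visit is likewise labelled for both arms. The week-5 visit is described for one arm only: "at week 5, which is the evaluation-point of treatment for GSH CBT-E (T1").

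The section on intervention and procedure states: "All participants will receive GSH CBT-E", with the control group beginning after a 12-week wait. The description of the programme then says of its own fifth week: "During week 5, they will fill out assessment questionnaires, sent to them by a link". It does not name these questionnaires.

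The section on other study outcome measures treats alliance as a hypothesized moderator of the treatment effect. The Statistical analysis section lists alliance with the outcomes and continues: "therapeutic alliance will be reported as means (standard deviations); and effect sizes between the two conditions will be reported" as Cohen's d. No time point is given for alliance.

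**The concern.** The WAI asks the patient to rate the alliance with a therapist. A calendar counted from randomization places the two arms at different points of treatment from week 5 onwards, and before week 12 one arm has had no treatment at all. Two problems follow.

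First, an effect size for alliance between conditions at a shared week would compare people with a therapist to people without one, or people at different distances from the end of treatment. It would be printed beside the efficacy effect sizes and could be read as one of them.

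Second, alliance matters to the rationale of this trial. The Background cites it as improving efficacy and contrasts synchronous phone contact with e-mail. Before the week-12 endpoint only the immediate arm has a treatment alliance, so alliance and outcome can be related only within treatment courses. Such an analysis needs a rating taken during treatment, ahead of the outcome. The listed calendar provides one mid-treatment in the immediate arm only. In the waiting-list arm, the only listed rating between the start of treatment and follow-up coincides with the end of treatment. A rating not collected at that arm's week 5 cannot be recovered later.

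**Working it through.** The plan gives no computed figure on this point, so the check sets the calendar against the treatment periods.

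**Inputs**
- Listed visits for the online forms: trial weeks 0, 5, 12, 24, 36 (Assessment).
- Programme length: 12 weeks (Intervention).
- Start of treatment: taken as week 0 in the immediate arm, which agrees with the Trial design section calling week 12 its end of treatment; week 12 in the waiting-list arm (Waiting list control group).
- Contact during the wait: a call of at most 10 minutes every 6 weeks (Waiting list control group).

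**Formula**
- Immediate arm: treatment week = trial week.
- Waiting-list arm: treatment week = trial week − 12.

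**Result**

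| Trial week | Immediate arm, treatment week | Waiting-list arm, treatment week | Same phase, in treatment? |
|---|---|---|---|
| 0 | 0 (not begun) | −12 (not begun) | No: neither arm has begun |
| 5 | 5 (mid-treatment) | −7 (waiting) | No |
| 12 | 12 (end) | 0 (start) | No |
| 24 | 24 (12 weeks after end) | 12 (end) | No |
| 36 | 36 (24 weeks after end) | 24 (12 weeks after end) | No |

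Shared trial weeks that allow a like-for-like alliance comparison: 0 of 5.

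**The waiting-list arm's treatment week 5**
- 12 + 5 = trial week 17, which is not among 0, 5, 12, 24 and 36.
- Treatment weeks that the listed visits cover in both arms: 0, 12 and 24. Treatment week 5 is covered in the immediate arm only, which is 90 of the 180 planned courses before any loss.

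**Alignment on treatment time instead**
- End of treatment: trial week 12 (immediate) with trial week 24 (waiting list).
- Twelve weeks after treatment: trial week 24 (immediate) with trial week 36 (waiting list).
- These pairs exist, but they set the same treatment against itself, delivered 12 weeks apart. They describe alliance; they do not estimate an effect of the intervention.

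**Reach of the problem**
The primary endpoint is at week 12 after randomization, and the sample size rests on d = 0.47 for binge eating. Neither uses the WAI.

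**The case against.** The strongest reply has four parts.

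1. *The schedule may be finer than the prose.* The Assessment section refers to Figs. 1 and 2, which are not available here and may give timing by form and arm. This stands as a limit: the point concerns the prose, which is explicit and makes no exception for the WAI.

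2. *The waiting-list arm is assessed mid-treatment.* A reader might infer from the calendar that it is not. The documents do not support that. The programme has questionnaires in its own fifth week and everyone receives the programme, so waiting-list participants should fill in forms at about trial week 17. Nor does the text say that these are discarded. What remains is that it does not say whether they are trial data or include the WAI.

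3. *Cohen's d may not be meant for alliance.* Alliance is called a moderator, and a semicolon separates the means from the effect sizes, so description only is a possible reading. It is the less natural one, because alliance stands in the list to which the effect sizes refer and is not exempted. If description was intended, the correction is one of wording.

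4. *Equal weeks since randomization are the right basis.* This stands in full for the efficacy outcomes.

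Three further inferences should be resisted. Alliance is not without any valid time point, since treatment-aligned pairs exist. Analyses by module are not confined to the immediate arm: the module is chosen within the programme by everyone, and the waiting-list arm has forms at the start and end of its treatment. And neither an analysis of early change nor a pooled alliance-outcome association across arms is stated in the protocol, so no gain in precision should be claimed for adding week 17.

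**Conclusion.** The point holds as a limited but worthwhile correction. The common calendar is sound for the randomized comparison. It lists no trial assessment at trial week 17, the waiting-list arm's own week 5, and the text leaves open the status and content of the programme questionnaires completed then. The between-condition Cohen's d for alliance, on the natural reading of the Statistical analysis section, is not interpretable at any of the five shared weeks: the waiting-list arm has had no treatment up to week 12, and the arms are in different phases at weeks 24 and 36.

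This rests on three assumptions: that the missing figures do not already set WAI timing by arm, that treatment starts at weeks 0 and 12 as labelled, and that the effect-size clause covers alliance. The primary endpoint, the other outcomes at week 12 and the sample size are not touched.

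**What to change.** - Remove therapeutic alliance from the between-condition effect sizes. Report it descriptively by treatment week, for example treatment weeks 5 and 12. These are trial weeks 5 and 12 in the immediate arm and 17 and 24 in the waiting-list arm.
- Collect the WAI only once a participant is in treatment, and state the visits for each arm.
- Record the waiting-list arm's treatment-week-5 programme questionnaires, with the WAI, as trial data.
- State that alliance is analysed within treatment courses, as a non-randomized association.
- Keep weeks 0, 5 and 12 for the randomized comparison of the other outcomes.

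The cost is a change of wording in the Assessment and Statistical analysis sections and one online form set at trial week 17, most of which the programme already calls for. WAI requests to people who are not in treatment fall away.
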